**Figure 1 nur22469-fig-0001:**
[figure not shown]
KIADEKU Overall project and sub‐studies.

To develop the AI model in the technical sub‐study, a literature‐based minimal data set for wound documentation of PI and IAD was defined. Based on this, 1,555 existing wound images and associated characteristics were extracted from the hospital information systems of two German university hospitals. The study team validated, segmented, and annotated these images and characteristics, achieving consensus on wound type and classification. Subsequently, four AI network architectures were evaluated, and the model with the best performance for differentiating between PI and IAD was selected. This transformer‐based model's performance was systematically enhanced through additional methods of data pre‐ and post‐processing, augmentation techniques, and training methods. The performance of the developed AI model for binary differentiation of PI and IAD and wound classification was evaluated using accuracy and F1 score (Harmonic Mean of Precision and Recall) on a test data set. These processes are described in more detail in the technical sub‐study conducted by the Institute for Artificial Intelligence in Medicine (IKIM).

After the AI model training was completed, we integrated it into the WUNDERA® wound documentation application of the project partner sciendis GmbH and it is now being used in the clinical intervention sub‐study to assist nurses in differentiating, assessing, and documenting PI and IAD wounds, and to facilitate personalized, evidence‐based nursing interventions. In a further qualitative sub‐study, the project partners at University Hospital Essen involve patients, wound experts, and nurses from both hospitals in the development of the AI, exploring their experiences and perspectives on the AI‐based application using group Delphi methodology and case vignettes.

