### Objectives

2.1

The primary objective of this sub‐study is to explore the relationship between the use of the AI‐based application and several factors: the duration of wound assessment, dressing changes, and documentation; the nurse's task load; and adherence to guidelines. We will adjust for potential covariates such as wound severity, the nurse's professional experience, and the general workload of the shift. A secondary objective is to evaluate the accuracy of the AI predictions regarding wound type and classification in a clinical setting, as well as the usability of the AI‐based application and standard clinical documentation systems.

Our hypothesis, which we intend to test, is that the use of the AI‐based application will enhance the differentiation, assessment, and documentation of PI and IAD by reducing the time required for wound assessment, dressing changes, and documentation; lowering nurses’ task load; and improving guideline adherence.

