### Setting

2.4

We are conducting the study at LMU University Hospital, a center renowned for its high‐end medicine, nursing, medical innovation, and research. With over 2,000 beds, LMU Hospital is a highly advanced hospital that encompasses all fields of medicine.

For this study, we selected four intensive care units, one intermediate care unit, and three general wards. These wards were chosen due to their notably high incidence of patients with pressure injuries (PI) or incontinence‐associated dermatitis (IAD), reflecting the specific diseases treated and the demographics of their patient populations. These wards differ in terms of medical specialty and the number of staff, ranging from 33 to 54 employees (average 45.8) in the intensive care and intermediate care units, and from 15 to 28 employees (average 23) in the general wards. The nursing and ward managers agreed to participate in this study. In addition, consent was obtained from the Staff Council, the Data Protection Officer, and the Ethics Committee of the LMU Medical Faculty. Additionally, before the commencement of the study, we confirmed that the selected wards had adequate Wi‐Fi coverage to support the use of the AI‐based application on tablets and smartphones.

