### Recruitment

2.7

A dedicated electronic wound reporting system will be utilized to identify wounds that meet the inclusion and exclusion criteria. Due to the absence of an electronic reporting system for IAD and the likelihood that many wounds are not electronically documented, the research team will contact the included wards daily by telephone. They will inquire about new cases of PI or IAD or the admission of patients with existing PI or IAD wounds. Each patient is only included once in the study.

If wounds that meet the inclusion and exclusion criteria are identified, the study team will arrange for the next scheduled wound care appointment. At this appointment, the study team will inform the patient's nurse about the study. If the nurse in charge declines participation, no observation or survey will be conducted at that time. Still, the patient may be re‐enrolled at the next wound care appointment if the subsequent nurse agrees to participate. If the nurse consents in writing to participate, the study team will proceed with the observation of wound care and documentation. After completing the wound documentation, the nurse will complete an online questionnaire on a tablet, which includes questions about demographic data, general workload of the shift, task load, and the usability of the documentation system used. The study primarily targets new wounds and newly admitted patients with wounds. Due to organizational factors, there may be delays in some cases, including weekend admissions, nurses refusing to participate, and delayed documentation of new wounds.

To encourage participation, we engaged local wound experts and ward managers in the development of the digital system in the KIADEKU qualitative sub‐study and as key users during its implementation on the wards to enhance user acceptance. Additionally, nurses who agree to participate will receive vouchers as compensation for the extra effort involved in the study. These measures are anticipated to help achieve the sample size determined by the a priori sample calculation.

After careful consideration, obtaining patient consent was deemed unnecessary. This decision was based on the fact that wound management in the study aligns with standard practice, with the only variation being the documentation tool used. Furthermore, the study does not collect data that could identify patients. Nonetheless, the study team informs patients about the study before administering wound care.

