The selected criteria include performing a finger pressure test or the transparent disk method in the presence of redness (recommendation 9.1), accurately assessing wound type and classification (recommendation 9.2), applying wound edge protection in cases of macerated wound edges or surrounding skin (recommendation 3.1), and ensuring pressure relief for pressure injuries (recommendations 5.1 and 5.5). The response options for these criteria are binary: ‘No’ or ‘Yes or not required’. Sum scores are calculated from the responses, assigning a score of 1 to ‘Yes or not required’ and a score of 0 to ‘No’. Interrater reliability is also measured in the study. Additionally, the nurse's task load during wound assessment, dressing change, and documentation is evaluated using the standardized and validated NASA TLX questionnaire (Human Performance Research Group n.d.).

Other covariates measured include the nurse's professional experience, wound severity, and the general workload of the shift, which is assessed on a 5‐point scale relative to the average.

To assess the accuracy of the AI predictions of wound type and wound classification in the clinical setting, the wound is independently assessed on‐site by a member of the study team, separate from the nurse's assessment and the AI prediction. This assessment serves as the ground truth for calculating the accuracy of the AI predictions regarding wound type and classification.

Additionally, the usability of the documentation systems used, namely the standard clinical documentation systems and the AI‐based digital system, will be assessed in both the control and intervention groups. Usability will be evaluated using the two‐item UMUX Lite questionnaire with a 7‐point Likert scale (Lewis et al. 2013) because of its brevity (Borsci et al. 2020) and comparability with other studies and the SUS scale (Lewis et al. 2013).

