### Analysis Plan

2.12

Once data collection is complete, we will use multiple linear regression models to examine the effects of the AI‐based digital system on the duration of wound assessment, dressing change, documentation, perceived task load, and guideline adherence. We will calculate an individual linear regression model for each dependent variable and incorporate potential covariates such as the nurses’ professional experience, wound severity, and the general load of the shift. Nominal and ordinal variables (use of the AI demonstrator, severity of the wound, general burden of the shift, and guideline adherence) will be dummy coded. We will then assess each model for linearity, homoscedasticity, and the absence of multicollinearity to satisfy the assumptions of linear regression. If these conditions are met, we will proceed with standard multiple linear regression, incorporating all independent variables as predictors. The f‐test will be used to examine the extent to which the independent variables predict the dependent variable, with R² indicating how much of the variance in the dependent variable can be explained by the independent variables. The t‐test will assess the significance of the predictors. To determine the specific contribution of the use of the demonstrator, we will calculate the explanatory power for both the full regression model and a reduced model without the demonstrator use variable, using the difference in explanatory performance to isolate the effect attributable to the demonstrator use. Datasets with missing socio‐demographic data for nurses, used only to describe the sample and not part of the statistical analysis, will still be included in the analysis. However, datasets with missing values for independent variables will be excluded entirely, and datasets with missing values for dependent variables will be excluded only from the specific model where the data is missing. The significance level is set at 0.05. As this is an exploratory study and a separate model is calculated for each dependent variable, no correction for alpha error is required. To analyze the interrater reliability of the observers, we will use Kendall's rank correlation coefficient (Kendall's tau). To determine the performance of the AI‐based application in the clinical setting, we will calculate its accuracy in predicting wound type and wound classification, using the on‐site assessment of a study team member as ground truth. Additionally, we will descriptively evaluate the usability of both the standard clinical documentation systems and the AI‐based application in terms of central tendency, variability, and distribution.

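### Accuracy is the only metric named for the AI in clinical use; it depends on an unstated PI/IAD mix, so recall for each wound type should be reported and should carry the conclusion

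*Protocol article*

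**What the plan says.** The Objectives section sets the aim: "A secondary objective is to evaluate the accuracy of the AI predictions regarding wound type and classification in a clinical setting". Under Measures, a member of the study team assesses the wound on site, independently of the nurse and the AI: "This assessment serves as the ground truth for calculating the accuracy of the AI predictions regarding wound type and classification". The Analysis Plan then fixes the summary: "we will calculate its accuracy in predicting wound type and wound classification". The sections on objectives, measures and analysis name no other performance metric for the clinical setting. They mention no recall by wound type, confusion table or interval.

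The Background describes the separate technical sub-study, in which the model "was evaluated using accuracy and F1 score (Harmonic Mean of Precision and Recall) on a test data set". The authors therefore use accuracy as a specific metric beside F1, and the clinical plan keeps only the first.

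The article gives no expected or target split of PI and IAD. Wounds enter as they are found on the participating wards.

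**The concern.** The application exists to help nurses tell PI from IAD. The Background says that misjudging these wounds can lead to unsuitable interventions and delay. The useful question is therefore whether the AI recognises each type.

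Accuracy does not answer that. It averages the two recalls with the enrolled proportions as weights, so it describes the case mix as well as the model. If one type is a clear minority, a model that often fails on it can score as well as one that handles both. The same model would also score differently on wards with another mix. In a pilot meant to guide further development, the reader would not learn which class fails.

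**Working it through.** **Inputs.** The metric (accuracy) is from the Analysis Plan. The article gives no figure for the AI's clinical accuracy, its precision or the PI/IAD mix, so there is no stated figure to reproduce. The assumptions are an IAD share q of 10% to 50%, illustrative recalls, and 48 AI-assessed wounds. The 48 is about half of the 95 planned nurses (half of 85 to 95 is roughly 42 to 48); the article gives no split by phase. Recruitment states that "Each patient is only included once in the study", so simple binomial intervals are a reasonable working basis.

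**Formulas.**
- Accuracy = (1 − q) × recall for PI + q × recall for IAD.
- Balanced accuracy = (recall for PI + recall for IAD) / 2.
- A rule that always answers PI scores 1 − q.
- A model that misses half of the IAD wounds can score at most 1 − 0.5q.

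**Worked case, q = 20%.**
- Recalls of 95% (PI) and 50% (IAD): 0.80 × 0.95 + 0.20 × 0.50 = 0.76 + 0.10 = 86%.
- Recalls of 86% and 86%: 86%.
- Always PI: 80%.
- Balanced accuracy for the three: 72.5%, 86% and 50%.

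**Across the mix.**

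| IAD share q | 95%/50% model | 86%/86% model | Always PI | Ceiling if half of IAD is missed |
|---|---|---|---|---|
| 10% | 90.5% | 86% | 90% | 95% |
| 20% | 86% | 86% | 80% | 90% |
| 30% | 81.5% | 86% | 70% | 85% |
| 40% | 77% | 86% | 60% | 80% |
| 50% | 72.5% | 86% | 50% | 75% |

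The 95%/50% model moves by 18 percentage points with no change in the model. At 10% IAD it outscores the even-handed model. From 30% IAD upwards it scores visibly lower. The ceiling shows when masking is possible: missing half of the IAD wounds is compatible with 90% accuracy only if q is at most 20%, and with 85% only if q is at most 30%. If PI were the minority, the same would hold with the classes exchanged.

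**In counts: 48 wounds, 10 of them IAD.**
- Model A: 5/10 IAD and 38/38 PI correct, so 43/48 = 89.6%.
- Model B: 9/10 IAD and 34/38 PI correct, so 43/48 = 89.6%.
- Both have the same exact 95% interval for accuracy, 77.3% to 96.5%.
- IAD recall is 50% (18.7% to 81.3%) for A and 90% (55.5% to 99.7%) for B. Balanced accuracy is 75% and 89.7%.
- Always PI: 38/48 = 79.2%.

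**Would F1 solve it?** For the 95%/50% model, F1 for IAD = q / (1.5q + 0.05(1 − q)). This is 0.51 at 10% IAD, 0.59 at 20% and 0.65 at 50%. F1 also moves with the mix.

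**The case against.** The best defence is that the article does not say accuracy will be the sole or pooled figure. A fuller plan could add class-specific results, and a journal article need not list every table for a secondary descriptive measure. Accuracy at the mix met on these wards is also a legitimate quantity for an objective framed in a clinical setting. No threshold or decision depends on it, and the confusion table can be produced at reporting in any case.

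Much of this stands, and it limits the point to a secondary objective. It does not remove the point. The Analysis Plan names the metric by which performance will be determined, and for the aim of differentiating two types a better one is available at almost no cost.

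Four stronger readings are tempting, and the documents do not support them:
- *The clinical result cannot be compared with the technical sub-study.* The test set was also evaluated by accuracy, so a comparator of the same kind exists, though it too depends on its mix.
- *Case-finding skews the mix against IAD.* Recruitment does give "Due to the absence of an electronic reporting system for IAD and the likelihood that many wounds are not electronically documented" as the reason for the daily telephone calls, but those calls ask about both PI and IAD. No shift in the mix is shown.
- *The classification figure counts wound-type errors twice and blends two systems.* The article does not say whether classification is scored jointly with type, within each system, or conditional on type.
- *Restoring F1 would cure the problem.* It would not, as the working shows.

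**Conclusion.** The point holds in a limited form. Accuracy is the only metric the article names for the AI in clinical use. It depends on a PI/IAD mix that is neither stated nor fixed, and by itself it cannot show whether each wound type is recognised. At an assumed 20% IAD, the 95%/50% and 86%/86% models are indistinguishable at 86%, only 6 points above always answering PI.

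A reader might infer that the trial's accuracy figure will hide a poor model. That does not follow: the mix is unknown, and near a balanced mix a model missing half of the IAD wounds could not exceed 75% and would be noticed. Dependence on the mix holds whenever the two recalls differ; masking needs an unbalanced mix as well. The mix, the recalls and the 48 wounds are assumptions. The regression models for duration, task load and guideline adherence are unaffected.

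**What to change.** Amend the Analysis Plan as follows.

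1. Report the PI/IAD confusion table, with recall for PI and recall for IAD, each with a Wilson or exact 95% interval, and balanced accuracy.
2. Show overall accuracy beside the majority-class rate in the same wounds.
3. Base the statement on differentiating PI from IAD on the two recalls.
4. Report classification agreement separately within the PI system and the IAD system, over all wounds of that reference type. Give agreement among correctly typed wounds only as a supplement, because that subset is selected on the model's own success.
5. F1 may be added for continuity with the technical sub-study, with a note that it also varies with the mix.

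The cost is wording: everything comes from the prediction and reference pairs already being collected, and the Discussion describes the intervention phase as still under way. The drawback is precision. With 48 wounds and 60% to 80% PI assumed, IAD recall rests on about 19 to 10 wounds (48 × 0.40 = 19.2; 48 × 0.20 = 9.6). Its interval will be wide, which is a fair picture of what a pilot of this size can show.

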## Discussion

3

This study protocol outlines a non‐randomized controlled trial designed to evaluate the effects of an AI‐based application on nursing wound assessment, care, and documentation, including its accuracy in predicting wound type and classification in a clinical setting. By integrating this application into nursing practices, we anticipate reductions in the duration of these processes, a decreased task load for nurses, and increased adherence to guidelines.

The technical feasibility of AI‐supported wound assessment and documentation has been established in recent studies (Ohura et al. 2019), as well as the technical evaluation (Howell et al. 2021) and its positive effects on the quality of wound documentation, wound healing, and patient compliance (Barakat‐Johnson et al. 2022). However, research into the application of AI in nursing has been limited, with few studies exploring its clinical potential beyond development (O'Connor et al. 2023). To our knowledge, the KIADEKU overall project is the first research and development project to explicitly incorporate nursing guidelines and specific nursing requirements in the development of an AI‐based application. In this interventional sub‐study, we adopt a user‐centered approach to evaluation, primarily exploring the AI's potential to support nurses in managing and documenting wound care while enhancing guideline adherence.

The selection of standardized and validated questionnaires such as the NASA TLX (Hart 2006) and UMUX lite (Borsci et al. 2020) to measure nurses’ task load and the usability of the documentation systems ensures high quality and comparability with other studies. Since no suitable instrument exists to measure guideline adherence in wound care observation, we identified specific criteria in an expert workshop to ensure both construct and content validity. These criteria informed our definition of standardized observation procedures and criteria to maintain objectivity.

Potential challenges in implementing the AI‐based application in a clinical setting include technical issues, such as ensuring full Wi‐Fi coverage, and meeting hygiene requirements, such as disinfecting tablets. Another common hurdle in technology intervention studies is user acceptance. However, in the realm of technologies that support nursing tasks, studies have shown high technology acceptance (Zöllick et al. 2020). We therefore anticipate high acceptance due to the simplification of wound care and documentation processes. To further enhance user acceptance, local wound experts and ward managers have been involved in the development of the application and will be key users during its implementation on the wards. Additionally, the implementation will be supported by comprehensive training measures to ensure safe use and handling of the application and AI predictions. This is crucial, especially when addressing incorrect or inaccurate predictions made by AI and the ethical challenges that arise in biomedical AI (Mittelstadt et al. 2016).

As this study is monocentric, focusing only on nurses at one university hospital, the external validity is limited. Another limitation is the constrained resources of the project, which preclude the use of a randomized study design and may introduce slight biases due to the consecutive and non‐randomized observation of control and intervention groups, as well as the absence of blinding. Moreover, the organization of information events and recruitment of nursing staff may heighten awareness of pressure injury and IAD care, potentially influencing care and documentation and thus the results of the study. Organizational delays, which are inevitable due to clinical processes, may also introduce bias. We also acknowledge that factors such as ward affiliation might influence outcomes, but were not included in this exploratory pilot study due to the complexity of the models required and the limited sample sizes. For this reason, only the most crucial factors, from an expert perspective, were included in the analysis.

This study is an exploratory pilot study. Further research is required to draw general conclusions about its potential to support nursing wound management, particularly regarding patient‐related outcomes and the impact on nurses’ critical thinking and workflows. Additionally, we aim to enhance understanding of AI and the valuable contributions nurses can make with their data, and to actively involve nurses in the development and implementation of AI to realize its potential in nursing.

As for the current progress of the study, data collection for the control group was completed in January 2024. Following the development of the AI and its integration into the prototype demonstrator, nurses from the selected wards were trained, and data collection for the intervention group commenced in July 2024. This phase of data collection is still ongoing and is expected to be completed by spring 2025. To date, no adjustments to the intervention study methodology have been necessary.

In conclusion, this interventional pilot study investigates the potential of AI in nursing wound assessment, management, and documentation. The findings could contribute to the further development of AI applications in nursing wound care and other nursing scenarios.

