### Design

2.3

The study is designed as a monocentric, non‐randomized, controlled pilot intervention study with a pre‐intervention data collection period followed by a data collection period during the deployment of the AI‐based application (intervention) on the wards. Due to the nature of the intervention, it is not possible to blind either participants or observers.

In the pre‐intervention phase, we observe the wound care and documentation for PI and IAD according to hospital standards in the control group, using a standardized observation form, and survey the nurse using a standardized questionnaire (Figure 2). In the subsequent intervention phase, we train the nurses in the intervention group to use the AI‐based application, then observe and survey the wound care and documentation supported by the AI‐based application, consistent with the procedures used in the pre‐intervention phase (Figure 2). The reporting of the study protocol is based on the SPIRIT AI extension (Cruz Rivera et al. 2020).

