### Data Collection and Management

2.11

The pre‐intervention data collection period began in May 2023 and continued until the required sample size was reached in January 2024. Following the completion of AI development in the technical sub‐study, we began training nurses and initiated the intervention phase with the corresponding observations and surveys in July 2024. Observations, on‐site wound assessments, and surveys of the nurses are conducted by trained nursing scientists using a digital questionnaire on tablets through the Lime Survey tool (Limesurvey GmbH 2024). The collected data is anonymized and stored on secure, access‐restricted servers available only to the research team.

To ensure that the documentation created can be linked to the observations while maintaining data confidentiality and security, a unique identifier is generated in the AI‐based application and recorded on the observation sheet. Neither this ID nor the data collected during the wound documentation, observation, and survey can be used to identify the patient or nurse. All collected data is stored in a password‐protected folder accessible only to the study team. Consent forms and confirmation of receipt of the voucher are stored securely and are also only accessible to the study team. Upon completion of data collection, the data will be exported and statistically analyzed using SPSS version 28.0.0.0 (IBM Corp 2021). Given the study's small sample size, relatively low complexity, and clearly defined endpoints, the establishment of a data monitoring committee is not deemed necessary.

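### Application use is the same variable as study phase, so the planned comparison cannot isolate the application's effect, and nothing supports calling the bias from consecutive observation slight

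*Protocol article*

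**What the plan says.** The Design section (2.3) describes a "monocentric, non‐randomized, controlled pilot intervention study with a pre‐intervention data collection period followed by a data collection period during the deployment" of the application. Section 2.11 gives the dates: "The pre‐intervention data collection period began in May 2023 and continued until the required sample size was reached in January 2024", after which the team "initiated the intervention phase with the corresponding observations and surveys in July 2024". The Discussion adds that this second phase "is expected to be completed by spring 2025".

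Sections 2.6 and 2.12 specify one linear regression per outcome with four predictors: use of the demonstrator, professional experience, wound severity and shift workload. Section 2.12 then compares R² between the full model and a model without the demonstrator term "to isolate the effect attributable to the demonstrator use". Section 2.1 states a directional hypothesis that the study intends to test, and section 2.12 sets the significance level at 0.05.

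On bias, the Discussion says that the lack of randomisation "may introduce slight biases due to the consecutive and" unrandomised observation of the two groups. It adds that information events and "recruitment of nursing staff may heighten awareness of pressure injury and IAD care, potentially influencing care and documentation", and so the results. Section 2.8 expects hospital infrastructure and wound-care processes to stay unchanged during the study.

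**The concern.** The phases do not overlap, and no standard-care observation is made after January 2024. The demonstrator indicator is 0 throughout the first phase and 1 throughout the second. Anything that differs between the phases and is not carried by the three covariates enters its coefficient and cannot be told apart from the application.

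Two statements in the article do not fit this. Section 2.12 says that the effect of the demonstrator will be isolated, which this design cannot do. The Discussion grades the bias from consecutive observation as slight, yet no figure or argument in the article supports that size.

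At stake is the meaning of a significant result for duration, task load or guideline adherence. The t-test on the demonstrator term tests whether the phases differ after adjustment. A favourable background shift can look like an application effect, and an unfavourable one can hide a real effect.

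**Working it through.** **1. The plan's own figure.** Section 2.6 assumes a moderate effect, alpha 0.05, power 0.80 and four predictors. Moderate is taken as f² = 0.15 (assumption; the number is not printed). The overall F-test with 4 and N − 5 degrees of freedom and noncentrality f²·N gives N = 85, power 0.803. With 10% loss, 85 / 0.9 = 94.4, so 95. Both stated figures are reproduced, and N = 85 is used below.

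**2. Timing.** Count months from 1 May 2023. Control observations lie in months 0 to 8 or 9. Application observations start at month 14 and end at about month 22 to 25 (assumed range for spring 2025).
- Start to start: 14 months.
- Unobserved gap: 14 − 9 = 5 to 14 − 8 = 6 months.
- Midpoint to midpoint: 13.5 to 15.5 months.

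**3. What the coefficient estimates.** If the outcome shifts between phases by D residual SD for reasons outside the three covariates, the demonstrator coefficient estimates (application effect + D). The R² difference does not separate the two. For a single added term it equals (1 − R² of the full model) × t² / residual df, so it is a re-expression of the same t statistic.

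**4. Size, for an assumed D.** Assumptions: N = 85, about 1:1, four predictor columns, no application effect, two-sided alpha 0.05. The standard error is about 2/√85 = 0.217 SD, so the noncentrality is D × √(85/4) = 4.61·D on 80 df. A simulation (6,000 runs per scenario, 42 and 43 nurses, three covariates, linear drift) serves as a second check.

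| D (SD) | Noncentral t | Simulation |
|---|---|---|
| 0 | 5.0% | 5.0% |
| 0.1 | 7.4% | 7.6% |
| 0.2 | 14.9% | 14.9% |
| 0.3 | 27.7% | 26.8% |
| 0.5 | 62.4% | 60.3% |

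**5. Would a calendar-time term solve it?** With uniform recruitment within each phase, the correlation between application use and month is 0.93 to 0.95, a variance inflation factor of 7.7 to 10.2. In the simulation the standard error of the application term rises from 0.220 to 0.642 SD, a factor of 0.642/0.220 = 2.9. Power for d = 2·√0.15 = 0.775 falls from 93% to 22% (analytically, from 94% to between 20% and 25%). The adjustment also relies on a straight line across a gap without data.

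**6. Can the control phase show the drift?** Take 42 observations uniform over 9 months. The SD of month is 9/√12 = 2.60, so the slope has standard error 1/(2.60 × √42) = 0.059 SD per month. Over 14 months this is 0.83 SD, with a 95% interval of about ±1.6 SD. Drifts of 0.1 to 0.5 SD cannot be resolved.

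**7. Drift needed to overturn a result.** Significance is lost at D = |b| − 1.99 × 0.217 = |b| − 0.43 SD. An observed difference of 0.775 SD would tolerate a favourable drift of about 0.34 SD, and one of 0.5 SD only about 0.07 SD.

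**The case against.** The limitation is disclosed. The Discussion names consecutive observation, lack of randomisation and blinding, awareness and organisational delays. It calls the study an exploratory pilot, gives limited resources as the reason for not randomising, and asks for further research before general conclusions. Section 2.8 gives some reason to expect a stable background. The wording in 2.12 can be read as dividing explained variance between the demonstrator and the covariates, not as a claim that time trends are removed. The drift values above are assumed, and any before-after study of this size would show similar rates.

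Much of this stands, and it rules out several stronger readings that a reader might infer:
- *The model is wrong because it lacks a time term.* With phases that do not overlap, such a term would cost most of the power, so its absence is not the defect.
- *Every change over 14 months is credited to the application.* Fourteen months is start to start; the unobserved gap is five to six. Change that runs through experience, wound severity or shift workload is adjusted for.
- *Awareness builds up and so favours the application.* The article says only that awareness may rise. It biases the estimate only as far as it differs between phases, which is not stated.
- *Modest drift makes a false result likely.* At 0.2 SD about 85% of null studies would still be non-significant.
- *Nothing planned would reveal drift.* A fuller analysis plan is not shown, so this cannot be known.

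Disclosure does not settle the matter. The same article states a hypothesis to be tested, tests it at 0.05, assigns the difference to the demonstrator and grades the bias as slight. Section 2.8 is an expectation about infrastructure and processes; it is not evidence about staff behaviour.

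**Conclusion.** The point holds as one of over-attribution and understatement, not of concealment or a wrongly chosen main model. From the article's own dates, application use is fully confounded with phase. The demonstrator coefficient and the R² difference estimate an adjusted difference between phases. Neither the claim to isolate the application effect nor the grading of the bias as slight follows from the design.

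The identity of application use and phase needs no assumption. The size does: it rests on N = 85, a split near 1:1, and assumed shifts of 0.1 to 0.5 SD, which give false-positive rates of about 7% to 61%. These rates illustrate sensitivity; they do not predict drift on these wards. The article reports data collection as still under way with analysis to follow, so as documented the wording can be changed before results are known.

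**What to change.** 1. In section 2.12, replace the wording about isolating the demonstrator's effect with a statement that the model estimates the adjusted difference between the standard-care and application phases.
2. In the Discussion, delete the word slight and state that no application effect is concluded from this coefficient alone.
3. Keep the planned regression as the main analysis. For each outcome, report beside the 95% CI the between-phase drift, in residual SD units, at which the result would lose significance. This is the CI limit nearest zero divided by the residual SD, so it needs no dates and no further modelling.
4. If observation month is retained (the article does not say), within-phase trends and a model with a linear month term may be shown as descriptive sensitivity analyses only. State their imprecision: a standard error of the application term about 2.9 times larger, and a control-phase trend uncertain by roughly ±1.6 SD over 14 months.

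Cost: changes of wording, one extra figure per outcome and, at most, a few extra regressions. No new nurses, patients or observations are needed. The price is more cautious conclusions and slightly longer reporting.
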